## Abstract

**Background:**

The benefits of physical activity are well-documented, and healthy habits established in childhood often continue into adulthood. Recent research has shown that schoolyards provide a valuable platform for children to be physically active, with greener spaces in particular enhancing both physical and mental well-being. The City of Stockholm has formally decided to reconstruct 20 schoolyards, incorporating more play areas and greenery. This study will evaluate the impact of these reconstructions, aiming to increase physical activity levels among schoolchildren across all socioeconomic groups, while also contributing to climate change mitigation in urban environments.

**Methods:**

This study will utilize a stepped-wedge design, where each school undergoing schoolyard reconstruction will serve as both a control and intervention site. Over four years, from 2024 to 2027, five schools will have their schoolyards reconstructed each summer. Control data will be collected in the spring prior to the reconstruction, with follow-up data collected in the spring after the reconstruction. We aim to recruit 3 600 children aged 6 to 12 years. The primary outcome will be changes in physical activity, measured via accelerometers. Secondary outcomes will include changes in musculoskeletal fitness, perceptions of the schoolyard, and environmental impact. Given the 24-hour constraint of daily time, movement behaviors (e.g., MVPA, LPA, SB, and sleep) will be treated as compositional data. Log-ratio transformation will be applied and introduced as outcomes in general linear mixed models, with schools treated as random effects.

**Discussion:**

This large-scale study has the potential to set new guidelines for physical health policies in schools across the City of Stockholm, potentially influencing the well-being of an even greater number of children. Additionally, the study could provide valuable insights into strategies for mitigating climate change through urban design, offering a model for sustainable school environments that promote both health and environmental resilience.

**Trial registration:**

The trial has been registered on ClinicalTrials.gov the 19th of May 2023, with the reference number NCT05865782.

**Supplementary Information:**

The online version contains supplementary material available at 10.1186/s12889-026-26609-9.

## Background

The health benefits of a physically active lifestyle during childhood are well-documented and include for example improved cardiometabolic health, mental health, sleep and positive effects on weight maintenance [1].

Establishing healthy physical activity behaviors in childhood may track into adulthood [2]. Moreover, traditional cardiovascular risk factors such as childhood levels of body mass index (BMI) and systolic blood pressure are associated with the development of incident adult cardiovascular events [3]. As such, primary prevention aiming at establishing healthy physical activity behaviors in young childhood may have long-lasting effects on chronic disease risk in adulthood.

In spite of the growing awareness of the health benefits from physical activity, less than half of children and adolescence worldwide reach the guidelines for physical activity [4] – and the same holds true for Sweden. More than half of Swedish school children do not meet the current guidelines, with girls being less active than boys and children having a lower socioeconomic status being less active than their socioeconomically privileged peers [5]. Since elementary school participation is mandatory in Sweden, the school environment is a fundamental arena for establishing healthy physical activity behaviors on a population level, independent of socioeconomic factors.

A Cochrane review from 2021, including 89 studies, showed that school-based PA interventions can have a small effect on children’s MVPA levels during school-hours and that school recess is a key setting that can provide opportunities for children to spent time outdoors and play and be physically active [6]. Another review showed that school recess can contribute between 5% and 40% of children’s recommended daily PA levels and that the least physically active children accumulate most of their daily PA during recess [7]. Systematic review data from intervention studies (*n* = 13) show moderate evidence for an effect on children’s PA levels from the provision of play equipment and limited evidence for an effect of decreasing playground density [8]. Moreover, a Danish intervention study from 2020 showed that a schoolyard reconstruction (e.g., implementation of new play features in the schoolyard such as climbing walls, balance-bars, skating areas, trampolines, hills, ball game facilities etc.) may increase children’s time spent outdoors and device-measured PA levels [9]. A systematic review from 2021, including 6 intervention studies, show that schoolyard greening has an effect both on physical activity and socioemotional health outcomes for school children [10]. Taken together, these data support the importance of the schoolyard as an important setting to increase children’s PA levels.

Beyond the immediate health benefits, increasing greenery in urban areas also addresses broader global concerns. Due to human activity, health and environmental risks due to climate effects in urban areas are expected to increase, with subsequent profound negative health consequences [11]. Research has shown that green areas are a relatively simple and cost-effective strategy for climate adaptation such as air temperature regulation and pollution reduction [12]. Indeed, the current evidence show protective effects of greenspace exposure on aspects related to chronic disease risk, for example physical activity, sleep quality, mental health and immunity function [13, 14]. Moreover, planting trees with heavy foliage to increase shade of schoolyards may be an effective strategy to reduce schoolchildren’s exposure to excessive sun exposure and the development of melanoma [15]. Consequently, increasing green area coverage in cities, via schoolyard reconstructions with greenery, is a promising and novel strategy to mitigate climate changes in urban environments and improve short- and long-term population health.

A formal decision in the Stockholm City Hall was taken to reconstruct 20 Stockholm public schoolyards with increased greenery during the years 2024–2027, (five schoolyard reconstructions per year). The proposed project entails an evaluation of the 20 schoolyard renovations. This is a unique co-creation project between Swedish Cancer Society, Birthe & Per Arwidsson’s Foundation, the City of Stockholm and Karolinska Institutet with the ambitious aim to increase school children’s physical activity levels across all socioeconomic groups and mitigate climate changes in urban environments.

## Objectives

### Aims

The primary aim of this project is to examine the effectiveness of schoolyard reconstruction on schoolchildren’s physical activity levels. The secondary aims include examining the effectiveness of schoolyard reconstructions on children’s i) musculoskeletal fitness ii) psychosocial functioning iii) sleep iv) perception of the schoolyard quality v) screentime, as well as on vi) incidents in the schoolyard, vii) the cost-effectiveness of schoolyard reconstruction and, viii) the environmental impact of schoolyard reconstruction.

### Hypothesis

Our main hypothesis is that schoolyard reconstructions will increase physical activity levels in school children and that reconstruction components such as greater greening and the provision of play equipment will have the strongest association with children’s changes in health outcomes. We further hypothesize that the reconstructions will have a positive impact on schoolyard quality and on the urban environment.

## Materials and methods

### Study design and setting

The current study will be designed as a stepped-wedge intervention where schools undertaking schoolyard reconstruction will act as both control and intervention schools [16]. A cross-sectional sample of children in 1st to 6th grade will be measured annually in all participating schools. Children will not be tracked longitudinally; therefore, the pre- and post-intervention samples will not necessarily include the same individuals. As a result, we avoid the issue of individuals being older at follow-up. Each year, five schools located in Stockholm County will receive the intervention—schoolyard reconstruction—during the summer breaks of 2024, 2025, 2026, and 2027 (see Fig. 1). The schools will act as control sites during the spring before the reconstruction and as intervention sites in the spring after the reconstruction. This design allows us to adjust for within-school characteristics, as each school serves as its own control. Additionally, by scheduling data collection at similar time points before and after the intervention within each school, we seek to minimize the influence of seasonal variation, which may affect outcomes such as children’s physical activity levels [17]. Furthermore, a stepped-wedge study design [16], is susceptible to year-to-year variation, and will therefore be confounded by time [18]. To address this, the five schools receiving their baseline measurements during the same spring period in which the intervention schools receive their follow-up measurements will be included in the analysis, allowing us to adjust for temporal variation across years. This report follows the SPIRIT reporting guidelines [19], with a checklist provided in additional file 1.

**Fig. 1 Fig1:**
[figure not shown]
Time frame and study design of the project

### Sample size

We have calculated the sample size to be able to detect an effect for treating each intervention-control schoolyard reconstruction as an independent unit analyzed separately. Power calculations were based on MVPA as the primary outcome, with a target power of 0.90. A five minute change in MVPA has been suggested in previous meta-analysis to be a reasonable target a of clinical importance [20]. Under the assumption of a standard deviation of 20 min [5], a minimum of 70 children per school at each pre‑ and post‑measurement is required. Although the study will include 20 schools, this sample size ensures sufficient power for analyses conducted at earlier stages of the stepped‑wedge design, when fewer schools are available.

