### Statistical analysis

Descriptive characteristics of the participants will be summarized using summary statistics.

The unit of analysis will be children nested within schools using a random effect. Generalized linear mixed models will be used to analyze changes in time spent at different physical activity intensities and secondary outcomes, comparing measurements taken before and after the schoolyard reconstruction. When appropriate, compositional data analysis will be employed to examine all daily activity—physical activity, sedentary time, and sleep—behaviors collectively [30]. This approach treats these behaviors as interdependent parts of a finite whole (i.e., the 24-hour day), acknowledging that an increase in time spent in one behavior necessarily results in a decrease in one or more of the others. Rather than focusing on isolated changes (e.g., an increase in MVPA alone), compositional data analysis allows for the analysis of shifts in the balance among all daily behaviors. The compositional outcome will be expressed through isometric log-ratio transformations, which recognize that each behavior’s duration is meaningful only in relation to the others. For easier interpretation, isometric log-ratios will be back-transformed into minutes to illustrate how the intervention influences the distribution of time across movement behaviors.

Physical activity will be further analyzed by distinguishing between time spent during school hours, at recess, and outside of school hours. As described in the Study Design and Setting section, temporal variation across calendar years will be controlled by including a period-of-measure indicator together with the intervention indicator (pre- or post-intervention measure).

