### Time plan of the project

This project entails an evaluation of five schoolyard reconstructions per year, in total 20 schoolyard reconstructions over four years. The reconstruction process is estimated to take between three to four months during the summer break. The schoolyard reconstructions were originally scheduled for 2023–2026. However, due to a recent increase in reconstruction costs, the projects planned for 2023 was postponed to 2024. Consequently, the follow-up data collection for the first five schools will now take place the spring of 2025 as shown in Fig. 1.

The recruitment of participants began in May 2023 and follow-up measurements for the first group of schools will take place in spring 2025. The remaining schools are expected to follow to the time plan, with recruitment expected to be completed by spring 2028 (see Fig. 1). The trial has been registered on ClinicalTrials.gov the 19th of May 2023 with the reference number NCT05865782. This is the first version of the protocol. Any changes to the protocol will be communicated to the trial registry.

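### Seventy children per school per occasion do not give 90% power for one reconstruction analysed separately; at an assumed two-sided 5% the power is about 31%

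*Protocol article*

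**What the plan says.** The Sample size section describes a calculation made "treating each intervention-control schoolyard reconstruction as an independent unit analyzed separately". Its inputs are given in the same paragraph:

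- Outcome and power: "Power calculations were based on MVPA as the primary outcome, with a target power of 0.90".
- Effect: "A five minute change in MVPA has been suggested in previous meta-analysis to be a reasonable target".
- Variability: "Under the assumption of a standard deviation of 20 min".
- Result: "a minimum of 70 children per school at each" of the two measurements, before and after. The paragraph adds that this number also protects analyses made while only some of the 20 schools have been completed.

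No significance level is given, and the text does not say whether the test is one-sided or two-sided.

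Three other sections bear on the reading:

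- Time plan of the project fixes what one reconstruction is: "This project entails an evaluation of five schoolyard reconstructions per year, in total 20 schoolyard reconstructions over four years". One reconstruction is therefore one school.
- Study design and setting says that individual children are not followed and that each year's sample is cross-sectional, so the before-after comparison is unpaired.
- Statistical analysis describes mixed models: "The unit of analysis will be children nested within schools using a random effect", with an indicator for measurement period.

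**The concern.** A 5-minute difference with SD 20 min is a standardised effect of 0.25. An effect that small normally needs several hundred children per group for 90% power, so 70 per group looks too few for a comparison within one school.

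This paragraph is the article's only power justification, and the recruitment target is built on it: 70 is raised to 90 for non-participation, then 180 per school, then 180 × 20 = 3 600. As worded, it lets a reader treat a before-after result from a single schoolyard as 90% powered. If the true power is near one in three, a real 5-minute gain at one school would be missed about two times in three. A null local result could then be taken as evidence that the reconstruction did nothing.

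**Working it through.** **Inputs.** From Sample size: difference 5 min, SD 20 min, power 0.90, 70 children per occasion. From Study design and setting: independent before and after samples. Assumed, because it is not stated: two-sided alpha 0.05; looser choices are shown below.

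**Attempt to reproduce 70 for one school.** For two independent means, n per occasion = 2 × (z_alpha + z_beta)² × (SD/difference)².

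- z_alpha + z_beta = 1.960 + 1.282 = 3.2415.
- n = 2 × 3.2415² × (20/5)² = 2 × 10.507 × 16 = 336.2, so 337 by the normal formula. The t test gives 337.2, so 338.

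The stated 70 is not reproduced.

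**Power at 70 against 70.** Standard error = 20 × √(2/70) = 3.381 min. Then 5/3.381 = 1.479, and 1.479 − 1.960 = −0.481, which gives power 0.315 (0.312 by t test). If all 90 recruits per occasion supplied data, power would be 0.39.

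**What 70 would support.** Detectable difference at 90% power = 3.2415 × 3.381 = 10.96 min. For 5 min to be detectable, the SD would have to be 5/(3.2415 × √(2/70)) = 9.1 min.

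**Other assumptions, one school** (normal approximation):

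| Test | n needed for 90% | Power at 70 per occasion |
|---|---|---|
| Unpaired, two-sided 5% | 337 | 0.32 |
| Unpaired, one-sided 5% (or two-sided 10%) | 275 | 0.43 |
| Unpaired, one-sided 10% | 211 | 0.58 |
| Paired, SD of change 20, two-sided 5% | 169 | 0.55 (t test 0.54) |
| Paired, one-sided 5% | 138 | 0.67 |
| Paired, one-sided 10% | 106 | 0.79 |

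The paired rows do not fit the cross-sectional design and are there only for completeness. No row reaches 0.90.

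**Where 70 may come from.** At two-sided 5%, 338/5 = 67.6 per school, close to 70. Pooling k schools and treating all children as independent gives power 0.55 for two schools, 0.73 for three, 0.84 for four and 0.91 for five (350 against 350). With a looser alpha, fewer schools would land near the same number: 275/4 = 68.75 for four schools at one-sided 5%. In each case the figure for unpaired samples comes back only by pooling schools.

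**What the five-school figure leaves out.** It makes no allowance for clustering or for the period adjustment. The article gives no intracluster correlation (ICC), so the following values are assumptions. With a design effect of 1 + 69 × ICC, 0.91 falls to 0.72 at ICC 0.01 and to 0.57 at ICC 0.02. This design effect may overstate the loss, because each school is its own control.

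**The case against.** The best defence is that the unit is misdescribed and the arithmetic is sound. The design works in yearly sets of five schools, and the closing sentence on early analyses speaks of schools in the plural. If the unit was one five-school step, 70 is a reasonable rounding. This may well be what was computed. But the paragraph mentions neither five schools nor pooling. It speaks of units analysed separately and of numbers per school, and the time plan counts each school as one reconstruction. The five-school origin is an inference, and only the authors can confirm it.

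It is also fair that 31% is not the protocol's own figure, because alpha and sidedness are missing. The range for unpaired samples is 31% to 58%. The direction does not depend on the choice.

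A reader might infer three stronger things that the document does not support:

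- **That the sample size paragraph contradicts the analysis section.** Sizing a study for an early, smaller analysis and later pooling all schools in a mixed model is not in itself a contradiction, and the paragraph acknowledges that 20 schools will follow.
- **That twenty separate 5% tests are planned**, with a chance of 1 − 0.95²⁰ = 0.64 of at least one false positive. The Statistical analysis section lists no such tests.
- **That the main 20-school analysis lacks power.** Nothing above shows this. Nor does the paragraph show that it is adequate, since no power is given for that model.

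**Conclusion.** The concern holds for the power statement as written. For one reconstruction analysed separately, 5 min, SD 20 min and 70 children per occasion give about 31% power against the stated 90%, assuming a two-sided 5% test on independent samples. About 338 children per occasion would be needed, and about 11 min is detectable with 90% power. Looser alpha raises the power to at most 58% for unpaired samples, and even the paired variants stop at 79%.

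Whether the slip lies in the number or in the naming of the unit cannot be settled from the article. Either way the stated power, sample size and unit cannot all stand together. The error is in a statement that others may rely on when reading single-school or early results; it does not establish a shortfall in the full trial.

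**What to change.** Rewrite the Sample size paragraph as follows:

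1. Withdraw the claim of 90% power for a single reconstruction analysed separately.
2. Name the unit to which the calculation actually refers (for example, one yearly step of five schools, if that is what was done), and state alpha and sidedness.
3. Restate power for that unit and for the planned mixed model with period adjustment, allowing for clustering over a stated range of ICC values.
4. Present any single-school result as descriptive, with its confidence interval and a note that about 11 min is the difference detectable with 90% power at 70 per occasion (two-sided 5%).

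The recruitment target need not change for this. The cost is one rewritten paragraph, a recalculation for the mixed model, and a less favourable stated power. Only if the authors do want confirmatory inference for individual schools would the number of children itself become the problem.

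### The claim of sufficient power at earlier stages is not supported for the first stage, where the year-adjusted effect compares five schools with five different schools

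*Protocol article*

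**What the plan says.** In the Protocol article, the Sample size section builds the number from three inputs: "A five minute change in MVPA has been suggested in previous meta-analysis to be a reasonable target", "Under the assumption of a standard deviation of 20 min", and a calculation "with a target power of 0.90". From these it requires "a minimum of 70 children per school at each" of the two surveys. It describes the calculation as "treating each intervention-control schoolyard reconstruction as an independent unit analyzed separately", and then adds that "this sample size ensures sufficient power for analyses conducted at earlier stages of the" stepped-wedge design, when fewer than 20 schools are available. It states no significance level, ICC, design effect or period term.

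The analysis is described elsewhere. To deal with year-to-year change, Study design and setting says that "the five schools receiving their baseline measurements during the same spring period in which the intervention schools receive their follow-up measurements will be included". Statistical analysis nests children within schools by a random effect and says that "temporal variation across calendar years will be controlled by including a period-of-measure indicator" next to the pre/post indicator. Study population and recruitment counts two surveys per school (180 × 20 = 3 600 children), whereas Study design and setting speaks of yearly measurement in every participating school.

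**The concern.** The early-stage statement is a positive claim about power, so it can be checked against the analysis that the article itself describes. The sample-size inputs contain nothing about schools or years, yet the model has a term for each. The design is said to let each school serve as its own control. At the first stage, adjusting for year removes that advantage, and differences between schools enter the comparison in full.

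What is at stake is how a first report on five reconstructed schools is read. If it is presented as having about 90% power for 5 minutes, a null result would look like evidence of no worthwhile effect when the analysis may have had little chance of finding one.

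**Working it through.** **Inputs.** From Sample size: difference 5 min, SD 20 min, power 0.90, 70 per school and survey. From Study design and setting: five schools per wave, and separate samples of children before and after. From Study population and recruitment: two surveys per school. Assumed, because not stated: two-sided 5% level, ICC from 0 to 0.10, and correlation *c* of a school's effect between years of 1.0 (constant) or 0.8 (school-by-year variation). Power = Φ(5/SE − 1.96) unless a t reference is named.

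**1. Reproducing the 70.** n per survey = 2 × 20² × (1.960 + 1.282)² / 5² = 337 after rounding up. Over five schools, 337/5 = 67.4, so 68 per school against the stated 70. With 5 × 70 = 350 per survey, power is 0.911. The figure therefore fits five schools pooled, ICC 0 and no year term.

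**2. One school analysed separately.** SE = √(2 × 400/70) = 3.38, so power = Φ(1.479 − 1.960) = 0.315. The literal wording of the section does not give 0.90.

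**3. First stage, planned model.** The data are wave 1 before, wave 1 after and wave 2 before. Wave 1 after and wave 2 before share spring 2025; wave 1 before is alone in its period. Three cell means face three fixed parameters (two periods, one intervention effect), so the estimate is exactly wave 1 after minus wave 2 before.

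Write v = 400 × [ICC + (1 − ICC)/70] for the variance of one school's survey mean. Then Var = 2v/5 = 160 × [ICC + (1 − ICC)/70].

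- ICC 0: SE 1.51, power 0.91
- ICC 0.01: SE 1.97, power 0.72
- ICC 0.05: SE 3.19, power 0.35

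Solving for the ICC, power falls below 0.90 at about 0.0006 and below 0.80 at about 0.006. These are between-school SDs of 20√0.0006 ≈ 0.5 min and 20√0.006 ≈ 1.5 min. With a t reference on 8 df, power is 0.61 at ICC 0.01 and 0.28 at 0.05.

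**4. Later stages.** Let r = c × ICC / [ICC + (1 − ICC)/70], the correlation between a school's two survey means. Each shared spring gives one contrast with variance 2v/5, and neighbouring contrasts have covariance −rv/5. The best combination has variance:

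- second stage: (v/5)(1 − r/2)
- third stage: (v/5)(2 − r²)/(3 + 2r)

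Example at ICC 0.05, c = 1: v/5 = 5.086 and r = 0.787. The second-stage SE is √3.086 = 1.757, power 0.81. The third-stage SE is √1.536 = 1.240, power 0.98. In the final model wave 4's follow-up is alone in its year and adds nothing to the effect estimate, so the final precision equals that of the third stage.

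| ICC (assumed) | First stage | Second, c = 1 | Second, c = 0.8 | Third and final, c = 1 | Third and final, c = 0.8 |
|---|---|---|---|---|---|
| 0 | 0.91 | >0.99 | >0.99 | >0.99 | >0.99 |
| 0.005 | 0.81 | 0.99 | 0.99 | >0.99 | >0.99 |
| 0.01 | 0.72 | 0.98 | 0.98 | >0.99 | >0.99 |
| 0.02 | 0.57 | 0.95 | 0.93 | >0.99 | >0.99 |
| 0.05 | 0.35 | 0.81 | 0.76 | 0.98 | 0.95 |
| 0.10 | 0.22 | 0.61 | 0.54 | 0.91 | 0.82 |

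**5. Where the loss comes from.** Without year adjustment, a before/after comparison in five schools has variance (2v/5)(1 − r). With c = 1 a constant school effect cancels and power stays at 0.91 or above. With c = 0.8 it is 0.875 at ICC 0.01 and 0.73 at 0.05. Clustering alone is therefore not the cause. The loss needs between-school variance together with the year term, or school-by-year variance.

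**6. If schools are surveyed yearly.** First-stage power by measurement schedule:

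| Schedule | ICC 0.01, c = 1 | ICC 0.05, c = 1 | ICC 0.01, c = 0.8 | ICC 0.05, c = 0.8 |
|---|---|---|---|---|
| Wave 2 schools also have an earlier baseline (10 schools) | 0.80 | 0.72 | 0.77 | 0.52 |
| All 20 schools surveyed each spring | 0.93 | 0.875 | 0.91 | 0.70 |

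**The case against.** The strongest reply has three parts. First, the article gives no ICC, and at ICC 0 the year-adjusted first stage still has 0.91, so the claim cannot be called false outright. That stands, and the shortfall is shown as a range. ICC 0 is nevertheless hard to reconcile with the article, which says that activity differs by socioeconomic status and that schools were chosen to represent different socioeconomic circumstances.

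Second, the first-stage result depends on two surveys per school, while another section describes yearly measurement. This also stands in part. With all 20 schools surveyed each spring, the first stage would reach 0.93 at ICC 0.01. But the recruitment total of 3 600 provides for only two surveys per school.

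Third, the article speaks of earlier stages in the plural, and a reader might infer that the claim fails at all of them. The figures do not support that: the second stage meets 0.90 up to an ICC of 0.02, and the third is as precise as the final analysis.

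A reader might also infer that early analyses inflate the type I error. The article does not establish this. It gives no schedule of looks and no stopping rule, and calls none of the early analyses confirmatory; such rules may stand in an analysis plan that is not shown. Nor does it suggest that early results would steer later reconstructions, since the city had already decided on all 20.

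**Conclusion.** The statement of sufficient power is unsupported for the first stage under the analysis that the article plans, and for any single school analysed alone (about 0.32). On the two-survey design, first-stage power is below 0.90 for any ICC above about 0.0006 and lies between 0.72 and 0.22 for ICCs of 0.01 to 0.10. At the second stage the answer depends on the ICC. From the third stage on, power is at least 0.91 up to ICC 0.10 with constant school effects, and at least 0.82 with a between-year correlation of 0.8, so the main 20-school result is not put in doubt.

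These figures rest on an assumed two-sided 5% level, assumed ICCs, 70 analysed children per school and survey, and mostly a normal approximation, which is optimistic with so few schools. The number 70 itself is not an arithmetic slip. It answers a simpler question than the one the model will be asked.

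**What to change.** - Withdraw the early-stage power claim for the first stage and for single-school analyses, and correct the wording that presents each reconstruction as a unit analysed on its own.
- Restate power by stage, and for the final 20-school year-adjusted model, over an ICC range such as 0.01 to 0.10 and with school-by-year variation. State the significance level used.
- Report first-stage results as estimates with intervals rather than as an adequately powered test.
- Reconcile Study design and setting (yearly measurement in all schools) with Study population and recruitment (two surveys per school), because first-stage power depends on which holds.

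The cost is one recalculation and some rewording, with no added recruitment. The downside is that early results lose their claim to adequate power.
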